# Effects of Bushen-Jiangya granules on blood pressure and pharmacogenomic evaluation in low-to-medium-risk hypertensive patients: study protocol for a randomized double-blind controlled trial

**DOI:** 10.1186/s13063-022-05999-2

**Published:** 2022-01-15

## Abstract

**Introduction:**

Hypertension is one of the most important risk factors for cardiovascular disease, and its control rates remain low worldwide. The most effective strategy is that patients with hypertension should be diagnosed and treated early. Preliminary studies showed that the Bushen Jiangya granule (BSJY) could suppress ventricular hypertrophy and inflammatory responses, lower blood pressure, and protect the target organs of hypertension. We designed a randomized, double-blind, placebo-controlled trial to evaluate the efficacy of BSJY in patients with low-to-medium risk hypertension.

**Methods and analysis:**

This trial is a one-center, randomized, double-blind, placebo-controlled study. A total of 260 participants will be randomized in a 1:1 ratio to an experimental group (BSJY plus amlodipine) and a control group (placebo plus amlodipine). The trial cycle will last 8 weeks. The primary outcome is the change in 24-h average systolic and diastolic blood pressure. The secondary outcomes include heart rate variability, pharmacogenomic evaluation, improvement in TCM syndrome, and serum pro-inflammatory/anti-inflammatory cytokines between the two groups. The safety of medication will also be evaluated. All the data will be recorded in electronic case report forms and analyzed by SPSS V.22.0.

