#### Secondary outcomes

The following are the secondary outcomes:
Heart rates variability, based on routine 24-h BP monitoringAssessment of any improvement in TCM Syndrome, using TCM Syndrome Integral Scale (Additional file 2). In this scale, the score of the symptom will be based on the severity, duration, and frequency of the symptoms: 0 points means the symptom did not appear in the past 1 month, 1 point means the symptoms are mild or the frequency of attacks is low, 2 points means the symptoms are moderate or the frequency of attacks is moderate; and 3 points means the symptoms are very severe or the symptoms constantly puzzled. The TCM therapeutic effect Index (TCMTEI), as calculated with the following formula, will be used to evaluate the treatment efficacy in the TCM syndrome.
$$ \mathrm{TCMTEI}=\left(\frac{\mathrm{symptom}\ \mathrm{score}\ \mathrm{before}\ \mathrm{treatment}-\mathrm{symptom}\ \mathrm{score}\ \mathrm{after}\ \mathrm{treatment}\ }{\mathrm{symptom}\ \mathrm{score}\ \mathrm{before}\ \mathrm{treatment}}\right)\times 100\% $$Assessment of any improvement in quality of life, using the 36-Item Short Form Health Survey [50, 51].Changes in levels of blood lipids, including total cholesterol, triglycerides, low-density lipoproteins, and high-density lipoprotein.Serum pro-inflammatory/anti-inflammatory cytokines in patients: changes in the serum levels of TNFα, IL2R, IL6, IL8, IL10, and IL1β will be assessed at baseline and treatment endpoint.Pharmacogenomic evaluation: twenty loci/SNPs associated with BP/hypertension will be assessed at baseline and treatment endpoint.Safety evaluation: routine blood and urine test including levels of creatinine, blood glucose, and homocysteine will be assessed at baseline and treatment endpoint.

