### Data collection and management

The case report form (CRF) will be used for recording the process for each participant. In addition to the enrollment evaluation (− 7 ± 0 days), each participant will attend an evaluation visit when allocated and every 2 weeks afterwards during the trial (0 days, 2 weeks, 4 weeks, 6 weeks, and 8 weeks). The assessments including physical examination, improvement in symptoms, compliance with medications, questions about adverse events will be given to each participant. Blood tests and 24-h BP monitoring will be evaluated only at the enrollment and close-out visits. The schedule of enrollment, interventions, and assessments can be checked in Table 2. All researchers involved in data entry and data management will sign a confidentiality agreement to prevent data leakage. The personal information of all participants will be carefully protected, and the original CRF will be kept for 5 years after the end of the trial.

**Table 2 Tab2:** Schedule of the data collection

Process/item	Run-in period	Run-in period	Pre-treatment	Treatment period			
Time point	− 7 day	− 1 day	0 days	2 weeks	4 weeks	6 weeks	8 weeks

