**Effectiveness observation**							
Blood pressure	√		√	√	√	√	√
24-h blood pressure			√				√
Pro-inflammatory/anti-inflammatory cytokines			√				√
Improvement in TCM syndrome			√	√	√	√	√
Improvement in quality of life			√				√
Pharmacogenomic evaluation			√				√

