**Safety observation**							
Physical exam		√					√
Blood pressure		√					√
Routine blood test		√					√
Routine urine test		√					√
Liver and kidney function		√					√
Adverse event				√	√	√	√

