### Statistical analysis

#### Sample size calculation

The formula used to calculate the sample size is as follows, which is based on superiority clinical trial interval hypothesis test sample size estimation [52]. The sample size was calculated based on the expected reduction in reducing of BP. One previous study suggested that the reduction of BP after interventional treatment is 4.5 mmHg, and the BP SD is 10 mmHg. Therefore, we assume the reduction of BP as 4.5 mmHg in this study. In the following formula, *c* is the ratio between two sample cases, *n*1 = *n*2, so *c* = 1. *σ* is the BP SD 10 mmHg, and *δ* is the expected effect BP 4.5 mmHg, so *σ* = 10 and *δ* = 4.5. Given a type I error rate of *α* = 0.05, a power of 90% (type II error rate of *β* = 0.1), so *uα* = 1.96, *uβ* = 1.282. *n1* = *n2* ≈ 104, the sample size for one group needs to be 104, resulting in *n* = 2 × 104 = 208 patients. Considering the maximum possible dropout rate is 20%, a total of 260 patients needs to be allocated to reach the required number of patients for the efficacy analysis.
$$ {\displaystyle \begin{array}{c}{n}_1={\left[\frac{\left( u\alpha + u\beta \right)\sigma }{\delta}\right]}^2\frac{\left(1+c\right)}{c},{n}_2=c{n}_1\\ {}{n}_1={n}_2\approx 104\end{array}} $$

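### Heart rate variability is a secondary outcome, but its only stated source, routine 24-h BP monitoring, does not on the ordinary reading deliver conventional HRV

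*Protocol article*

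**What the plan says.** In the abstract (Methods and analysis), HRV comes first among the secondary outcomes: "The secondary outcomes include heart rate variability, pharmacogenomic evaluation, improvement in TCM syndrome". The Secondary outcomes section also puts it first and adds where it comes from: "Heart rates variability, based on routine 24-h BP" monitoring. No index follows.

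Data collection and management limits the recording to two occasions: "Blood tests and 24-h BP monitoring will be evaluated only at the enrollment and close-out visits". Table 2 has a row "24-h blood pressure" under effectiveness, ticked at day 0 and week 8. Neither its effectiveness rows nor its safety rows include an ECG, a Holter recording or HRV itself.

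The article does not describe the 24-h monitor, its reading interval or its recording principle.

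**The concern.** HRV, as the term is normally understood, is calculated from consecutive beat-to-beat intervals. Routine ambulatory BP monitoring ordinarily takes intermittent readings and stores one heart rate with each. The name of the outcome and its source therefore do not fit together.

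This goes beyond a detail that an analysis plan could fill in. An analysis plan can choose an index, but it cannot supply beat-to-beat data that were never recorded, and here the protocol itself fixes the source.

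If the plan is followed as written, the spread of a few dozen heart rates per day would be reported under the name HRV. A change in night-time heart rate or in daily activity could then show up as changed HRV, while a real change in short-term beat-to-beat variability could go almost unseen. The meaning of the outcome would also remain open to choice after the data are known.

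**Working it through.** **Step 1: what the text fixes.**
- Outcome name: heart rate variability (abstract; Secondary outcomes).
- Source: routine 24-h BP monitoring (Secondary outcomes). No second source is named.
- Index: none. By contrast, the Primary outcome section names an index for blood pressure, a 24-h coefficient of variability, which intermittent readings can support.
- Beat-to-beat recording: none in the text or in Table 2.

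**Step 2: the plan's own figure.** The sample size rests on blood pressure ("so *σ* = 10 and *δ* = 4.5"). With u values 1.96 and 1.282, n = 2 × [(1.96 + 1.282) × 10 / 4.5]² = 103.8, so 104 per group and 208 in all. Allowing for 20% dropout, 208 / 0.8 = 260. It reproduces, and it does not depend on HRV.

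**Step 3: how different the two quantities could be.** The documents give no inputs for this, so all of the following are assumptions:
- one reading every 15 to 30 min, mean rate 70/min;
- two thirds of readings by day (p = 2/3);
- day-night difference D = 10 or 15 bpm;
- within-period SD w = 6 or 8 bpm;
- beat-level SD 3.5 bpm, averaged over about 10 effective independent beats per reading.

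Number of values: 1440/30 = 48 to 1440/15 = 96 readings, against 70 × 1440 = 100,800 beats.

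Variance of the readings: T = p(1 − p)D² + w² + b, with b = 3.5²/10 = 1.225. Multiplying the beat-level SD by 1.5 adds 1.225 × (1.5² − 1) = 1.531 to T, so the SD of the readings changes by √[(T + 1.531)/T] − 1.

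| D | w | T | Day-night share | Beat-level share | Rise in SD of readings |
|---|---|---|---|---|---|
| 10 | 6 | 22.2 + 36 + 1.225 = 59.4 | 37% | 2.1% | 1.28% |
| 10 | 8 | 22.2 + 64 + 1.225 = 87.4 | 25% | 1.4% | 0.87% |
| 15 | 6 | 50 + 36 + 1.225 = 87.2 | 57% | 1.4% | 0.87% |
| 15 | 8 | 50 + 64 + 1.225 = 115.2 | 43% | 1.1% | 0.66% |

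The figure of 10 effective beats largely sets the last two columns. At the extreme of no averaging at all, b = 12.25 and the added term is 15.31. T then runs from 22.2 + 36 + 12.25 = 70.5 to 50 + 64 + 12.25 = 126.25, and the rise from √(141.56/126.25) − 1 = 5.9% to √(85.8/70.5) − 1 = 10.3%. That is still far below 50%.

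**The case against.** The strongest reply is that the device is unknown. That it uses a cuff and stores intermittent rates is general measurement knowledge applied to the phrase about routine monitoring; the article does not say so. A monitor with an ECG channel is not excluded, and a journal article may leave the device to the full protocol. This stands, and the conclusion must be conditional on the ordinary reading.

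A reader might infer that the outcome cannot be measured at all. The documents do not support that. An SD or coefficient of variation of the monitor's heart rates can be computed, and the authors may mean exactly this, by analogy with the BP variability listed as a primary outcome. In that case the data exist and the label is what misleads.

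A reader might also take the missing ECG row in Table 2 as proof that no other source exists. It is weak evidence, because blood lipids, glucose and homocysteine are listed as outcomes or safety measures and have no row of their own either. The weight rests on the source stated in the Secondary outcomes section.

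Nor does the plan announce an autonomic claim. The Objectives and the Discussion mention neither HRV nor autonomic function. Misreading is a risk created by the term, not a planned conclusion.

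Finally, no input to the illustration comes from the trial. The model also treats day-night variation as foreign to HRV, whereas the SD of all beat intervals over 24 h, a standard whole-day index, contains it. The contrast therefore applies to short-term indices.

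**Conclusion.** The point holds as a mismatch between the name of a secondary outcome and its only stated source. If the monitor takes intermittent readings, conventional HRV is not obtainable from it. The spread of its heart-rate readings is obtainable, but that is a different quantity, driven partly by day-night and activity differences. On either reading of the authors' intent something needs correcting: the label, if they mean the spread of readings, or the stated recording and index, if they mean conventional HRV.

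The reach is limited to one of several secondary outcomes. The numerical size is illustrative and rests wholly on assumed inputs; the qualitative conclusion rests only on the ordinary meaning of routine 24-h BP monitoring and of HRV.

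**What to change.** In the abstract and in the Secondary outcomes section, replace heart rate variability with mean ambulatory heart rate (24-h, daytime and night-time) and the reading-to-reading SD of heart rate within daytime and within night-time. Computing the SD within each period takes the day-night step out of it. State that these measures will not be interpreted as HRV or as autonomic function. If the monitor in use does record beat-to-beat intervals, keep the outcome and name that recording and the HRV index instead.

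The cost of renaming is wording only: no data, visit or device changes. The trial gives up an HRV label that its stated source does not support. According to Trial status, recruitment was continuing and no analysis had been conducted at manuscript submission, so on that account the definition could still be fixed before results are seen.

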**Ethics and dissemination:**

This study has been approved by the Research Ethics Committee of Guang’anmen Hospital, China Academy of Chinese Medical Sciences in Beijing, China (No. 2019-186-KY-01). The participants are volunteers, understand the process of this trial, and sign an informed consent. The results of this study will be disseminated to the public through peer-reviewed journals and academic conferences.

**Discussion:**

We hypothesize that patients with low-to-medium-risk hypertension will benefit from BSJY. If successful, this study will provide evidence-based recommendations for clinicians.

**Trial registration:**

Chinese Clinical Trial Registry ChiMCTR1900002876. Registered in November 2019

**Supplementary Information:**

The online version contains supplementary material available at 10.1186/s13063-022-05999-2.

## Strengths and limitations of this study

This is the first randomized, double-blinded, placebo-controlled clinical trial that explores the efficacy, safety, and pharmacogenomic evaluation of Chinese medicine (BSJY) in treating patients with low-to-medium-risk hypertension.Numerous experiments and case studies showed that BSJY had a good effect on lowering BP and improving quality of life. However, there is a lack of high-quality clinical research on the supposed benefits of BSJY.The complexity of the genetic mechanisms underlying hypertension and the need for much larger sample sizes when looking for genes associated with BP should be considered. For BSJY, it can be viewed as a very important environment element to pharmacogenomic evaluation.The multi-center experiments should be conducted in the future.

## Introduction

Hypertension is one of the most important public health issues due to its association with a number of serious diseases, including cardiovascular disease and stroke. According to the 2020 International Society of Hypertension (ISH) Global Hypertension Practice Guidelines, although effective management greatly reduces the risk of cardiovascular events, blood pressure (BP) remains uncontrolled in many people [1–3]. This ISH guide is different from the past, mainly in the following three points: (1) different BP goals: the best standard is that for young and middle-aged people, the target BP should be less than 130/80 mmHg (not less than 120/70 mmHg); (2) the grading of hypertension is simplified and reduced the three stages to the two main ones (stages 1 and 2); and (3) adjust the risk stratification, cancel the very high risk, and merge it into the high risk. BP remains uncontrolled in a number of people. If the diagnostic criteria for hypertension are moved forward, the BP of more people can be managed, which will help prevent long-term complications and reduce the long-term burden of economic health [4]. Although the new US guidelines advocate the priority lifestyle intervention for the hypertensive population with the new definition, there are big differences in implementation and treatment in China and other Asian counties, and large-scale clinical trials are still needed to determine the ideal antihypertensive treatment, not only for the senior people, but also for the young and middle-aged population [5].

For the treatment of hypertension, five drug classes (β-blockers, angiotensin-converting enzyme inhibitors, angiotensin receptor blockers, thiazide diuretics, and calcium channel blockers) are considered appropriate first-line therapy for HTN [6]. However, uncontrolled BP and resistance are observed in more than 40% of the patients, and more than 75% of patients require prescribing combination therapies and various medications [7, 8]. The low efficacy of some therapies could be related to inter-individual genetic variability. Novel targets for hypertension should focus on treating treatment-resistant hypertension, improving BP control, and targeting the genetic, functional, and structural alterations associated with hypertension [9]. Pharmacogenomic evaluation of antihypertensive responses offers the clinical promise of individualization of therapy based on a person’s genetic makeup [10, 11]. More than twenty single nucleotide polymorphisms (SNPs) have been associated with BP in genome-wide association studies in Asian people [12, 13]. The loci/SNPs associated with BP/hypertension are also associated with BP response to antihypertensive drugs [8].

Traditional Chinese medicine (TCM) has long been widely used in hypertension in China. *Huangdi Neijing*, a classic work on TCM, classified hypertension as headaches and vertigo. Nowadays, numerous studies have demonstrated the biological activity and therapeutic mechanism of TCM in hypertension [14, 15]. Bu-Shen-Jiang-Ya granule (BSJY) is composed of eight herbs, Dihuang (Radix Rehmanniae Glutinosae), Shanzhuyu (Corni Fructus), Duzhong (Cortex Eucommiae Ulmoidis), Tianma (Gastrodiae Rhizoma), Sanqi (Notoginseng Radix), Mudanpi (Cortex Radicis Moutan), Shanzha (Crataegi Fructus), and Zexie (Rhizoma Alismatis), which is made from a modification of the classical Chinese herbal formula Liuwei Dihuang pill (Table 1). Our previous studies show that BSJY has a clinical effect on patients suffering from kidney-yin deficiency syndrome type hypertension [38–40]. The experimental acute toxicology study showed that the safety of BSJY is reliable [41]. Besides, BSJY reversed hypertensive ventricular hypertrophy by regulating the ERK pathway and protected the endothelial function by regulating the PI3K/Akt pathway [42]. However, the pharmacogenomic evaluation of antihypertensive responses of BSJY remains unclear. This study is designed to investigate whether BSJY may represent a potential remedy for decreasing BP and slowing disease progression in low-to-medium-risk hypertension based on pharmacogenomic evaluation. If positive, this work will be the first one that provides an evidence-based medicine remedy for TCM on treating hypertension by pharmacogenomic evaluation.

**Table 1 Tab1:** Components and dose of BSJY

Chinese name	English name	Latin name	Origin	Main ingredients	Main pharmacological effects	Raw drug weight (g)	Granule weight (g)
Duzhong	Eucommia bark	Cortex Eucommiae Ulmoidis	The bark of Cortex Eucommiae Ulmoidis	Quercetin; Mairin; beta-sitosterol; kaempferol; Erythraline; Eucommin A; (-)-Tabernemontanine; cyclopamine; GBGB; helenalin	Lowering BP [16]; reversing hypertensive vascular remodeling and hypertensive cardiac remodeling [17]; improving insulin resistance and lowering blood glucose [18]	10	0.48
Dihuang	Rehmannia	Radix Rehmanniae Glutinosae	The root of Radix Rehmanniae Glutinosae	EIC; sitosterol; stigmasterol; aeginetic acid; jioglutin D; rehmaglutin B	Lowering BP and improving insulin resistance [19] glucose metabolism, lipid metabolism [20]	25	3.57
Tianma	Gastrodia	Gastrodiae Rhizoma	The tuber of Gastrodiae Rhizoma	Daucosterol; citronellal; dauricine; gastrodin; p-hydroxybenzaldehyde; p-hydroxybenzyl alcohol; 4-hydroxybenzylamine; suchilactone; suffruticoside a; sucrose; vanillin; vanillin acetate	Impairing vascular endothelial function [21]; lowering BP [22]; improving lipid metabolism and insulin resistance [23]	20	1.82
Wuzhuyu	Cornus fruit	Corni Fructus	The fruit of Corni Fructus	Beta-sitosterol; sitosterol; stigmasterol; mandenol; ethyl linolenate; poriferast-5-en-3beta-ol; ethyl oleate (NF); leucanthoside; hydroxygenkwanin; telocinobufagin; gemin D; tetrahydroalstonine	Regulating adipogenesis [24]; lowering blood glucose and insulin resistance [25]; improving lipid metabolism [26]; protecting vascular endothelial cell [27] and protecting target organs and tissue related to diabetic damage [28]	10	1.43
Mudanpi	Cortex of the Peony Tree Rote	Cortex Radicis Moutan	The root and bark of Cortex Radicis Moutan	Quercetin; Mairin; sitosterol; kaempferol	Increasing the arterial blood flow, and improving glucose metabolism [29]; lowering BP and heart rate [30]	10	0.91
Zexie	Alisma	Rhizoma Alismatis	The rhizome of Rhizoma Alismatis	Sitosterol; alisol B; alisol B monoacetate; alisol,b,23-acetate; alisol B; alisol C; alisol C monoacetate; 1-monolinolein	Lowering blood glucose [31]; improving Hepatic lipid deposition [32]; improving lipid metabolism [33]	30	2.73
Sanqi	Notoginseng root	Notoginseng Radix	The root of Notoginseng Radix	Quercetin; beta-sitosterol; stigmasterol; mandenol; DFV; ginsenoside rh2; ginsenoside f2	Protecting the vascular endothelium [34]; improveing myocardial ischemia [35]	3	1.5
Shanzha	Crataegus fruit	Crataegi Fructus	The fruit of Crataegi	Quercetin; isorhamnetin; sitosterol; kaempferol; stigmasterol	Promoting anti-atherosclerosis [36]; improving vascular endothelial dysfunction [37]	30	4.29

## Methods and design

### Objectives

Our study aims to assess the clinical effect of BSJY on pharmacogenomics and pro-inflammatory/anti-inflammatory cytokines in patients with low-to-medium-risk hypertension, to firstly provide a preliminary pharmacogenomic evaluation of antihypertensive responses in hypertension, and to observe whether TCM plus Western medicine has a better curative effect than Western medicine alone.

### Study design

This protocol will be designed as a randomized, placebo-controlled trial. Participants, investigators, and statisticians will be blinded. A total of 260 subjects will be recruited at Guang’anmen Hospital of the China Academy of Chinese Medical Sciences in China. The trial will be implemented based on the principles of Good Clinical Practice and reported according to the CONSORT statement [43, 44]. The trial flow diagram is illustrated in Fig. 1. The Standard Protocol Items: Recommendations for Interventional Trials (SPIRIT) [45] Checklist is shown in Additional file 1. The SPIRIT-TCM Extension 2018 Checklist is shown in Additional file 3. This study has been registered at http://www.chictr.org.cn. (ChiMCTR1900002876).

**Fig. 1 Fig1:**
[figure not shown]
CONSORT flow diagram for BSJY clinical trial. BSJY, Bushen Jiangya granules

### Patient and public involvement

This trial was designed to evaluate the effect of BSJY on BP and pharmacogenomic evaluation in low-to-medium-risk hypertension. Our previous clinical practice showed that BSJY adding to routine medications may lower BP and improve life quality in essential hypertension patients. The primary and secondary outcome measures used in this trial were considered as important endpoints in clinical practice. However, the participants in this trial were not directly involved in the design, recruitment, or conduct of the study. After the trial is completed, the results of this study will be disseminated to the public through peer-reviewed journals and academic conferences. The burden of intervention will not be assessed by trial participants.

